#### Data management

All patient-reported questionnaires (SPADI, Pain Catastrophizing Scale, EQ-5D-5 L, Baseline and End of treatment) will be filled in by the patient in a paper format, and all data from the physiological measurements and clinical tests will be entered in a paper Case Report Form. Subsequently, all data will be entered in EpiData (version 3.1 or newer) by study personnel, using blinded double data entry to ensure data quality. The data entry form will support valid values and range checks where applicable. The original forms will be kept on file at a secure location on the study site for a period of 3 years after completion of the study. Data collected through SMS-track is entered directly by the participant as they send the answer in a text-message. The validity of data will be secured through answer validation, where answers that do not fit the specified requirements will be rejected. Reminder messages will be automatically generated in case of missing answers.

All data from the BandCizer units will be stored on the unit and transferred the BandCizer Backend Software (BandCizer^®^, Denmark) via Bluetooth connection to a dedicated repeater unit with internet access. All electronically entered data will be stored on a secure drive at the study site.

No data monitoring committee will be composed and no formal stopping guidelines and corresponding interim analyses are planned. No other interim analyses are planned.

### Allocation

Participants will be randomly assigned to either the control or intervention group (CG or IG) at a 1:1 allocation ratio, using a computer generated randomisation schedule of permuted blocks of random sizes ranging from 4 to 10.

Participants will be randomised using sequentially numbered, opaque, sealed envelopes. Investigators taking part in allocation and data collection will be blinded to block sizes and randomisation sequence at all times during the study period. Allocation concealment will be ensured, as the envelopes will not be opened before the participant has been irreversibly included in the study.

The creation of the randomisation schedule of permuted blocks of random sizes, and subsequent packaging of sequentially numbered, opaque, sealed envelopes will be performed by persons not else involved in the trial.

The final enrolment and subsequent allocation of participants will be conducted by investigators not taking part in any outcome assessment, who will be blinded to the randomisation sequence at all times during the intervention period. Outcome assessors will not take part in any of the processes related to allocation.

### Blinding

Outcome assessors performing the outcome assessment at baseline and follow-up weeks 5, 10 and 16 will be blinded to group allocation. Given the nature of the intervention, which requires the treating therapist to know the intervention, blinding of intervention providers is not deemed feasible, and therefore will not be performed. In order to obtain valid results from this trial, intervention receivers will be kept blind to treatment allocation. This will be attained through minimal information about the content of the add-on intervention and control condition until group allocation is final. Accordingly, participants will be informed (written and orally) that the study compares two different treatment regimens, and that both include the treatment elements normally offered, and adhere to the clinical guideline. Additionally, study participant will be strongly inculcated not to enclose or discuss treatment allocation with the outcome assessors, medical doctors or physiotherapists providing usual care.

All pre-defined analyses will be performed by a data analyst blinded to allocation.

#### Emergency unblinding

Investigators and caregivers will be encouraged to consult with the Medical Advisor (PH) in a case where unblinding seems relevant. As the intervention is only an add-on to usual care, and it will be modified with respect to the participants pain response, the probability of circumstances occurring where unblinding could be relevant seem very slim.

### Statistical methods – outcomes

For the primary end-point, namely SPADI score after 16 weeks, and for all continuous secondary outcomes listed in Table 2, a constrained linear mixed model (cLMM) will be applied in order to compare the change from baseline to 16 weeks in the IG to that in the CG. The model will contain the outcome at 16 weeks as the dependent variable, treatment group (IG or CG) as the main effect and both baseline score and any additional follow-up measurements as repeated measurements, to estimate the differences in mean change between groups and corresponding 95% confidence intervals (95% CI) (Table 3). The covariance structures will be selected based on the MAICE procedure [57].

**Table 2 Tab2:** Variables, outcome measures and methods of analysis

Variable/outcome	Hypothesis	Outcome measure	Methods of analysis
Primary outcome	Intervention improved outcome		
SPADI change Δt_0_-t_3_		Score 0–100 (continuous)	cLMM
Secondary outcomes	Intervention improved outcome		
Abd. MVC change Δt_0_-t_3_		Nm/kg (continuous)	cLMM
Ext. rot. MVC change Δt_0_-t_3_		Nm/kg (continuous)	cLMM
Abd. total ROM change Δt_0_-t_3_		Degrees (continuous)	cLMM
Pain last week change Δt_0_-t_3_		NRS 0–10 (continuous)	cLMM
EQ-5D change Δt_0_-t_3_		Index value (continuous)	cLMM
Global impression of change, at t_3_		% much improved/fully recovered (binary)	χ^2^ test
Pain sensitisation Δt_1_-t_3_			
Temporal Summation of Pain		VAS increase (continuous)	cLMM
Conditioned Pain Modulation		kPa increase (continuous)	cLMM
Pain Pressure Threshold		kPa (continuous)	cLMM
Scapular involvement			
SAT		% positive (binary)	χ^2^ test
SDT		% positive (binary)	χ^2^ test
Subgroup analyses			
Scapula involvement (SAT and SDT yes/no)	Dysfunction modifies the effect of intervention	SPADI score, abduction MVC and external rotation MVC (continuous)	cLMM with interaction term
Central sensitisation (TS and CPM high vs. low)	CS modifies the effect of intervention	SPADI score, abduction MVC and external rotation MVC (continuous)	cLMM with interaction term
Sensitivity analyses	Intervention improved outcome	Primary outcome	
Per protocol analysis			cLMM
Adjusting for baseline			cLMM

*cLMM* constrained linear mixed model, *EQ-5D* EuroQol 5D-3 L, *MVC* maximum voluntary contraction, *Nm/kg* Newton meter per kilo body weight, *ROM* range of movement, *SAT* scapula dysfunction, *SDT* scapula dyskinesia, *SPADI* Shoulder Pain and Disability Index, VAS visual analogue scale

**Table 3 Tab3:** Outcomes (Mean, SD)

	Week 0		Week 5		Week 10		Week 16	
	IG	CG	IG	CG	IG	CG	IG	CG
SPADI score								
Abduction MVC								
External rotation MVC								
Abduction ROM								
Pain last week								
QoL (EQ-5D)								

*CG* control group, *IG* intervention group, *MVC* maximum voluntary contraction, *QoL* quality of life, *ROM* range of movement, *SPADI* Shoulder Pain and Disability Index

Mean scores and corresponding 95% CIs will be reported for all outcome time-points (t_0_, t_1_, t_2_ and t_3_) (Table 3). Within group changes between all outcomes assessment time-points (t_0_-t_1_, t_1_-t_2_ and t_2_-t_3_), and between baseline and last assessment (t_0_ and t_3_), and corresponding 95% CI, will be reported (Table 4). Finally, differences in within group changes between all outcomes assessment time-points (t_0_-t_1_, t_1_-t_2_ and t_2_-t_3_) and the corresponding 95% CIs will be reported (Table 5). Results from the repeated measures analysis with SPADI score as outcome will be visualised as illustrated in Fig. 2.

**Table 4 Tab4:** Within group change scores (95% CI)

	Week 0–5		Week 5–10		Week 10–16		Week 0–16	
	IG	CG	IG	CG	IG	CG	IG	CG
SPADI score								
Abduction MVC								
External rotation MVC								
Abduction ROM								
Pain last week								
QoL (EQ-5D)								

*CG* control group, *IG* intervention group, *MVC* maximum voluntary contraction, *QoL* quality of life, *ROM* range of movement, *SPADI* Shoulder Pain and Disability Index

**Table 5 Tab5:** Between group difference in change scores (95% CI)

	Week 0 to 5 (95% CI)	Week 5 to 10 (95% CI)	Week 10 to 16 (95% CI)	Week 0 to 16 (95% CI)
SPADI score				
Abduction MVC				
External rotation MVC				
Abduction ROM				
Pain last week				
QoL (EQ-5D)				

*CG* control group, *IG* intervention group, *MVC* maximum voluntary contraction, *QoL* quality of life, *ROM* range of movement, *SPADI* Shoulder Pain and Disability Index

**Fig. 2 Fig2:**
[figure not shown]
Visualisation of changes in SPADI score in the intervention and control group, respectively (example, not based on data)

For comparison of binary outcomes, proportions will be compared using a χ^2^ test, and odds ratio estimates and corresponding 95% CIs will be reported.

Results from analyses comparing IG and CG for all primary and secondary outcomes will be reported in the second paper outlined in the ‘Dissemination policy’ section, except for the results on secondary outcomes regarding pain sensitisation and scapula dyskinesia, which will be reported in the third and fourth paper outlined in the ‘Dissemination policy’ section, respectively.

*P* values will be reported to the fourth decimal. For all tests, a two-sided significance level of ≤ 0.05 will be applied. All analyses will be conducted using up-to-date versions of SPSS and SAS.

#### Statistical methods – additional analyses

##### Subgroup analyses

For the outcomes SPADI score, abduction MVC and external rotation MVC, subgroup analyses investigating the modifying effect of scapula dysfunction, scapula dyskinesia, temporal summation of pain, conditioned pain modulation, pain pressure threshold (site 1) and pain catastrophizing, respectively, will be conducted. These will be performed using a cLMM, similar to the corresponding main analyses, but including a dichotomised value for the first measurement of the relevant variable as the interaction term and reporting the effect estimates for each subgroup.

The following sensitivity analyses will be performed for the primary outcome and reported together with the primary analyses in the primary trial report:A per protocol analysis, similar to the primary analysis, will be performed. From the IG, only patients who attended intervention appointments on weeks 0, 5 and 10 will be included in this analysis, while all patients in the CG will be included.Adjusted cLMM to adjust the effect of treatment allocation on SPADI score for any baseline differences between groups. Baseline variables will be included as covariates if (1) the difference between groups is more than 0.3 of the common SD for continuous outcomes, or (2) proportions are significantly different (*P* < 0.05) between groups, for binary outcomes.Sensitivity analyses to investigate the importance of the clinometric properties of the SPADI score may be relevant. This is based on a very recent study [58], which evaluates the SPADI score using the Rasch model. The study was published after initiation of this trial.

Three exploratory dose-response analyses will be performed. Only participants in the IG will be included in these analyses. First, the interacting effect of adherence to the intervention, TSP and CPM, on change in external rotation MVC, abduction MVC and SPADI score (outcomes), will be investigated. Secondly, whether the effect of TSP and CPM is mediated by adherence to the intervention will also be assessed. These analyses will be conducted as available-case analyses.

For all included variables, data from each time-period (t_0_-t_1_, t_1_-t_2_ and t_2_-t_3_) will be included as repeated measurements in these analyses. The outcome variable is the change between first and last measurement in a time-period. ‘Adherence’ to the intervention is the total TUT in a time-period. ‘Central Pain Sensitization’ score (TSP or CPM) is the score from the last time-point in each time-period.

Additionally, results will also be presented for similar analyses adjusted for Usual Care, calculated for each time-period as the average of time spent on usual care, as reported by text-message, in all weeks included in the relevant time-period.

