#### Secondary objectives

To investigate the effectiveness of adding a 16-week simple home-based shoulder strengthening exercise programme to usual care, compared to usual care alone, on changes in shoulder abduction and external rotation strength from baseline to end of treatment (16 weeks) in patients with SIS.To investigate the modifying effects of pain sensitisation, pain catastrophizing and scapula function on the effectiveness of adding a 16-week simple home-based shoulder strengthening exercise programme to usual care, compared to usual care alone, on changes in patient-reported shoulder function and shoulder abduction and external rotation strength from baseline to end of treatment (16 weeks) in patients with SIS.To investigate the dose-response relationship between objectively monitored adherence to the add-on intervention and change in patient-reported shoulder function, shoulder abduction strength and external rotation strength.To investigate the relationship between central and peripheral pain sensitisation and change in patient-reported shoulder function, shoulder abduction strength and external rotation strength, and to what degree this is mediated through adherence to the intervention.

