### Sample size

The sample size estimation is based on the primary outcome SPADI. Studies on patients with SIS have shown standard deviations (SD) for SPADI change score after 11–12 weeks of between 17 [12] and 18.5 [56], while longer durations seem to entail larger SDs, with a SD of 22 reported for SPADI change from 0 to 22 weeks [12]. The latter is similar to our own unpublished data from SIS patients, showing a SD of 22.5 for SPADI change from 0 to 6 months. Based on this previous data, we expect a common SD of 19.5 for SPADI change values from week 0 to 16, the primary outcome. For the purpose of this study, the MCID for SPADI will be considered to be 10 points, based on previous studies [45, 48]. The negative effect that any dropouts will have on the statistical power will, to some degree, be reduced by the use of multiple imputation. However, the imputation of data will not fully redeem this, as multiple imputation can cause an underestimation of the effect and a larger variation in outcomes. Therefore, we aim at having a high power of 95% to verify an effect equal to or higher than the MCID of 10 points on SPADI, at a 5% significance level. To obtain this, a total of 200 patients will be required (100 in each group). This corresponds to a power of 89.7% in case of a 20% dropout and a power of 85.4% in case of a 40% dropout.

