#### Statistical methods  – analysis population and missing data

All main analyses will be conducted as intention-to-treat analyses, including all randomised participants, regardless of protocol adherence. Participants will be analysed as randomised. To create a full analysis dataset for the intention-to-treat analyses, missing outcome data will be imputed using multiple imputations based on the variables of all previous scores in the relevant outcome, age, sex and allocation.

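### Read naturally, the subgroup interaction models use outcomes imputed without the modifier or its interaction with allocation, which biases the effect-modification estimates, usually towards zero

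*Protocol article*

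**What the plan says.** One of the secondary objectives is "To investigate the modifying effects of pain sensitisation, pain catastrophizing and scapula function" on the treatment effect for SPADI, abduction strength and external rotation strength. Under Subgroup analyses the protocol names six modifiers: scapula dysfunction, scapula dyskinesia, temporal summation of pain (TSP), conditioned pain modulation (CPM), pressure pain threshold (PPT, site 1) and pain catastrophizing. Each is examined with a cLMM "similar to the corresponding main analyses, but including a dichotomised value for the first measurement of the relevant variable as the interaction term".

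The section on analysis population and missing data makes the main analyses intention-to-treat on a completed data set, obtained by "multiple imputations based on the variables of all previous scores in the relevant outcome, age, sex and allocation". That list has no modifier and no modifier-by-allocation term, and no other imputation model is given.

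The one stated exception closes the paragraph on the dose-response and mediation analyses in the intervention group: "These analyses will be conducted as available-case analyses". The subgroup analyses carry no such sentence.

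**The concern.** An imputation model should contain every term of the analysis model it serves. Here it contains allocation but not allocation × modifier. Two patients with the same earlier scores, age, sex and arm therefore receive imputed week-16 values from the same distribution, whichever modifier group they belong to. Once the earlier scores are accounted for, the imputed values carry no further effect modification. An interaction fitted to observed and imputed values together is a blend of the true interaction and a weaker one. The bias does not shrink as the trial grows.

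At stake is the answer to a secondary objective. If rotator cuff loading really works less well in patients with, say, scapula dyskinesia, the procedure would tend to understate this, and more so the more outcomes are missing.

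**Working it through.** **Inputs from the protocol.** SD: "we expect a common SD of 19.5 for SPADI change values from week 0 to 16". Design target: "high power of 95% to verify an effect equal to or higher than the MCID of 10 points on SPADI", "at a 5% significance level", two-sided, with 100 patients per group. SPADI is collected at weeks 0, 5, 10 and 16. The only missing-data rates given are the 20% and 40% dropout scenarios under Sample size.

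**Assumptions not in the protocol.** True interaction 10 SPADI points; modifier split 50/50; equal correlation ρ of 0.5 or 0.7 between visits; missingness unrelated to outcome; modifier known for every patient. A week-16 regression adjusted for baseline stands in for the cLMM. Interactions are given as absolute sizes.

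**Step 1: the protocol's own figure.** n per group = 2 × 19.5² × (1.960 + 1.645)² / 10² = 98.8, so 99, against 100 stated. Power at 100 per group is 95.0% (t-test). The inputs reproduce the design.

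**Step 2: power for the interaction with complete data.** Four cells of 50 patients: SE = 19.5 × √(4/50) = 5.52. Power = Φ(10/5.52 − 1.96) = Φ(−0.147) = 44%.

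**Step 3: expected attenuation.** Let p be the fraction with week 16 imputed, and κ the share of the interaction that the earlier scores carry into the imputed values. Then

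estimate ≈ 10 × [(1 − p) + p × κ].

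- Only a baseline score: κ = 0. This gives 8.0 at p = 0.20 and 6.0 at p = 0.40.
- Only week 16 missing: each of the three earlier scores has regression weight ρ/(1 + 2ρ), which is 0.25 at ρ = 0.5. If the interaction builds up linearly (1/3 at week 5, 2/3 at week 10), κ = 0.25 × 1 = 0.25, giving 8.5 and 7.0. If it is fully present from week 5, κ = 0.25 × 2 = 0.50, giving 9.0 and 8.0.

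**Step 4: large-sample simulation** (400,000 patients per scenario, both values of ρ, both build-up patterns):

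| Dropout pattern | 20% dropout | 40% dropout |
|---|---|---|
| Baseline score only | 7.8–8.0 | 5.8–6.0 |
| Spread over visits | 8.1–8.7 | 6.5–7.6 |
| Only week 16 missing | 8.5–9.3 | 7.1–8.3 |

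This agrees with Step 3. With modifier and modifier × allocation added to the imputation model, every scenario returns 9.7 to 10.3. Using only patients with an observed week-16 score returns 9.8 to 10.3.

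**Step 5: trial-size simulation** (100 per group, ten imputations, Rubin's rules, 500 runs, linear build-up, dropout spread over visits):

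| Dropout | Listed predictors: mean, power | Modifier terms added: mean, power |
|---|---|---|
| 20% | 8.2, 24% | 10.1, 41% |
| 40% | 6.6, 11% | 9.6, 31% |

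At 20% with the listed predictors, the pooled SE is 5.9 against a true sampling SD of about 5.0, so the interval is also too wide. These models adjust for baseline, so their power should not be set directly against the 44% of Step 2, which uses plain change scores.

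**Step 6: a case in the other direction.** True interaction 0; modifier main effect 10 points; dropout after baseline of 30% in one arm and 10% in the other. Imputed values carry no modifier effect, so the apparent modifier effect is 0.7 × 10 = 7 in one arm and 0.9 × 10 = 9 in the other: a spurious interaction of 2 points. Simulation gives 1.95, and about −0.2 (within simulation error) once the modifier terms are included.

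**The case against.** The strongest objection is that the protocol never says the subgroup models use imputed data. Imputation is tied to the main analyses, the subgroup models sit under additional analyses, and being similar to the main analyses may refer to model form only. This stands as far as it goes: use of imputed data is an inference. It is still the natural one, because the modifier term is the only difference named and available-case analysis is reserved for the dose-response work. If it was not intended, the text needs a sentence to say so.

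A reader might also infer that every imputed patient is given no effect modification at all. That is true only of patients without any post-baseline score; week 5 and 10 scores pass part of it on (Step 3). Nor is shrinkage certain, as Step 6 shows.

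The figures for dropout before week 5 may not apply to TSP, CPM and PPT. Table 2 lists these as change from t1 to t3, and the protocol speaks of the first measurement rather than baseline. They may therefore first be measured at week 5 (the schedule figure is not shown). Patients lost earlier would then have no modifier value. With dropout only after week 5, trial-size simulation still gives about 8.4 at 20% and 7.2 at 40%.

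Finally, the size rests on an assumed interaction as large as the MCID. The 40% rate is a power scenario, not a forecast, and patients who withdraw from assessment visits are offered continued questionnaires. All of this limits the size, not the mechanism.

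**Conclusion.** The concern holds in a limited form. If the subgroup models use the imputed data, as the text is most naturally read, the interaction estimates are biased because the imputation model leaves out the modifier and its product with allocation. With similar dropout in both arms they are usually attenuated. Under the stated assumptions a true 10-point interaction is estimated at about 8 to 9 with 20% dropout and about 6 to 8 with 40%. With unequal dropout and a prognostic modifier, an interaction can appear where none exists.

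The documents do not support saying that the protocol explicitly prescribes imputed data here, that all modification is erased in every imputed patient, or that the bias must run towards zero. The primary analysis is untouched. With complete-data power of only about 44% for an interaction of this size, though, the modifier analyses have little to spare for an avoidable loss. The point should be corrected before analysis.

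**What to change.** Add one sentence under Subgroup analyses: the subgroup cLMMs are fitted to the observed repeated scores without imputation. The mixed model already uses every observed visit, so nothing else is needed.

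If imputation is kept, impute separately for each modifier, with the modifier and modifier × allocation in the imputation model, among patients whose modifier was measured. That last condition matters for TSP, CPM and PPT if they are first measured after baseline.

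In either case, report the interaction estimate with its 95% CI beside the subgroup-specific effects.

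Cost: one sentence and, at most, one extra imputation run per modifier. The small downside is that the number of patients in the subgroup models is described differently from that in the main analysis.

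### Four effect modifiers measured on scales (TSP, CPM, PPT, pain catastrophizing) are to be split in two for 12 of the 18 interaction tests, an avoidable loss of power on a stated secondary objective

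*Protocol article*

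**What the plan says.** Under Subgroup analyses (Statistical methods – additional analyses), the protocol article sets out the outcomes and the first modifiers: "For the outcomes SPADI score, abduction MVC and external rotation MVC, subgroup analyses investigating the modifying effect of scapula dysfunction, scapula dyskinesia". The sentence goes on to temporal summation of pain (TSP), conditioned pain modulation (CPM), pressure pain threshold at site 1 (PPT) and pain catastrophizing. The model is the same constrained linear mixed model as in the main analyses, "including a dichotomised value for the first measurement of the relevant variable as the interaction term and reporting the effect estimates for each subgroup".

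Table 2, under Statistical methods – outcomes, has two subgroup rows. One covers the two scapula tests, the other reads "Central sensitisation (TS and CPM high vs. low". PPT and pain catastrophizing have no subgroup row. The same section sets one threshold throughout: "For all tests, a two-sided significance level of ≤ 0.05 will be applied".

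Effect modification by pain sensitisation, catastrophizing and scapula function is listed under Secondary objectives. The sample size was set for the main effect only: "high power of 95% to verify an effect equal to or higher than the MCID of 10 points on SPADI".

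**The concern.** TSP is read on a 0–10 cm scale, CPM and PPT in kPa, and catastrophizing on a 0–52 score. Splitting such a variable treats everyone on one side of the cut as alike, and treats patients just either side of it as different. If the treatment effect changes gradually with the modifier, that discards information. Interaction is already the weakest-powered question in a trial sized for a main effect, so the loss falls where least can be spared. The article gives no reason for the split, and its own dose-response analyses use TSP and CPM as scores.

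At stake is the answer to a stated secondary objective, which is assigned to separate papers under Dissemination policy. The primary comparison is not affected.

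**Working it through.** **Inputs.** Sample size section: "a total of 200 patients will be required (100 in each group"), and "we expect a common SD of 19.5 for SPADI change values from week 0 to 16". Target difference 10 SPADI points, two-sided α = 0.05. Assumed here, because the article gives no figures: the distribution of each modifier, a linear modifying effect, and 19.5 as the residual SD.

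**The plan's own figure.** n per arm = 2(1.960 + 1.645)² × 19.5² / 10² = 98.8, so 99. The t-test version gives 99.8, so 100. With 100 per arm, power is 95.2% (normal) or 95.0% (t). The stated 200 is reproduced.

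**Count of tests.** 6 modifiers × 3 outcomes = 18. Modifiers on scales: 4 × 3 = 12. Modifiers that are yes/no by nature: 2 × 3 = 6. Table 2 as printed: 4 modifiers × 3 = 12, of which 2 × 3 = 6 use a split scale.

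**Information kept by a split.** This is the squared correlation between the modifier and its two-level version. For a normal modifier cut so that a fraction p lies on one side, it is φ(c)² / [p(1 − p)], where c is the cut on the standard normal scale:

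| Split | Kept | Lost |
|---|---|---|
| 50/50 | 63.7% | 36.3% |
| 40/60 | 62.2% | 37.8% |
| 25/75 | 53.9% | 46.1% |
| 20/80 | 49.0% | 51.0% |

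The median cut is the most favourable. For other shapes cut at the median:
- Uniform: (1/8)² / [(1/12)(1/4)] = 0.75 kept, 25% lost.
- Exponential: (0.5 × ln 2)² / 0.25 = 0.48 kept, about 52% lost.

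**Power for a 10-point SPADI interaction between halves, 200 patients.**
- Median split: 50 patients per arm in each half. SE = 19.5 × √(2/50 + 2/50) = 5.52. Power = Φ(10/5.52 − 1.96) = Φ(−0.15) = 44%.
- Same modification, modifier kept continuous: the mean modifier values of the two halves of a normal variable are 1.596 SD apart, so the slope is 10/1.596 = 6.27 points per SD. SE = 2 × 19.5/√200 = 2.76. Power = Φ(6.27/2.76 − 1.96) = Φ(0.31) = 62%.

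**Multiplicity, taken separately.** 18 × 0.05 = 0.9 expected false positives if no modification exists. If the tests were independent, the chance of at least one is 1 − 0.95¹⁸ = 60.3%. In a simulation with assumed correlations of 0 to 0.9 between outcomes and 0 to 0.5 between modifiers, it ran from about 32% to 60%. None of these figures depends on whether the modifier is split.

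**Timing.** Tables 3 to 5, read with the time-point labels, suggest t0 to t3 are weeks 0, 5, 10 and 16. Table 2 gives pain sensitisation as t1 to t3, whereas SPADI, strength, range of movement, pain and EQ-5D run from t0 to t3. Under Secondary outcomes, TSP, CPM and PPT are compared at week 16 and not as change from baseline. The first measurement of these three may therefore be at week 5. Fig. 1, which would settle it, is not shown in the text at hand.

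**The case against.** The strongest reply is that these are additional analyses with a formal interaction test, that no primary conclusion rests on them, and that they are underpowered however the modifier is coded. All of that is fair, and it limits the weight of the point. It does not justify giving up power that a change of coding would keep. A split could also do better if the true effect has a threshold near the cut, but the article claims no threshold for any of the four.

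Four stronger readings are tempting, and the document does not support them:
- A reader might infer that all 18 interactions lose information. Six do not, because the scapula tests are binary by nature.
- A reader might take a loss of at least a third as certain. It needs a roughly normal modifier, and the article gives no distributions; the uniform case loses 25%.
- A reader might infer that splitting makes a chance subgroup finding likely. A pre-set split costs power but does not raise the false-positive rate. The 60% is an upper figure under independence, and these tests share patients, related outcomes and related modifiers.
- A reader might count the absent cut-points as an error. They may stand in an analysis plan that is not shown, so they are no finding here.

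**Conclusion.** The concern holds as a point about efficiency. The article fixes a two-level coding for four scale modifiers in 12 of 18 interactions. Under a roughly normal modifier with a linear effect, this loses 36% or more of the information. For a 10-point SPADI interaction between halves at N = 200, it lowers power from about 62% to about 44%. The size depends on the assumed distribution, on linearity, on SD 19.5 applying to the residual, and on full follow-up.

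Three further points stand apart from the coding. The modifier lists differ (six in the text, four in Table 2). The document leaves it unclear whether TSP, CPM and PPT are first measured before randomisation; if they are not, treatment could already have affected them, and the interaction could not be read as modification by a baseline characteristic. Finally, 18 tests at 0.05, with 0.9 false positives expected under no modification, do not support a claim from one isolated small P value.

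**What to change.** 1. Enter the first measurement of TSP, CPM, PPT and pain catastrophizing as a continuous variable, with a treatment-by-time-by-modifier term and its lower-order terms. Report the week-16 treatment effect with 95% CIs at chosen percentiles, for example the 10th, 50th and 90th. Check linearity with a plot or spline, and use splits for display only. Keep the two scapula tests binary.
2. Give Table 2 and the Subgroup analyses text the same list of modifiers.
3. State at which visit TSP, CPM and PPT are first measured, and reconcile this with the t1 to t3 entry in Table 2. If that visit follows randomisation, say so and limit the interpretation accordingly.
4. State that the interaction results are exploratory, reported as estimates with CIs, with no claim from a single P ≤ 0.05.

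The cost is analysis wording only, with no added data or patients. The downside is the linearity assumption, which the plot or spline can check.
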